## **3. Materials and Methods**

### **3.1 Experimental Design**

This will be a parallel, prospective, randomized clinical trial. Only the volunteers will remain blinded to the allocation group (single-blind design).

A sample of 192 teeth with exposed hypersensitive root dentin will be planned, with 48 teeth per group. The study factors will be: (1) desensitizing treatment at four levels

(Table 1): fluoride varnish (positive control, Duraphat – VF); solution containing crystalline bioactive ceramic (Biosilicate® – SS); self-etch adhesive system (Single Bond Universal – SB); and light-cured fluoride varnish (VL); and (2) evaluation times: baseline (prior to treatments), and 7, 15, and 30 days, as well as 6 and 12 months post-treatment. The response variables will be hypersensitivity assessment through the Visual Analog Scale (VAS) and the Computerized Visual Analog Scale (CoVAS).

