### 3.2 Sample Size Calculation and Patient Selection

Sample size was calculated based on a published study using Sigma Plot 12.0 software, with an expected mean difference in cervical dentin hypersensitivity levels (measured by VAS) of 0.210 after six months. Test details: significance level ( $\alpha$ ) = 0.05; test power ( $1-\beta$ ) = 0.80; dropout ( $\beta$ ) = 0.2. The final sample size was determined as 48 teeth per group.

Patients will be recruited from the undergraduate clinic of FOA-UNESP, aged between 20 and 70 years, with at least one root exposure, totaling 192 teeth with DH in non-cavitated root exposures (not requiring restoration), regardless of location in the dental arch. Teeth will be divided into three groups ( $n = 48$  teeth each) with a 5% significance level. Eligibility criteria are described in Table 2.

**Table 1.** Products to be used in the study and their composition according to the manufacturers

| Material                                                                                                                                                                                                                                                                          | Manufacturer                                  | Composition*                                                                                                                                                                           | Application*                                                                                                                                                                             |
|------------------------------------------------------------------------------------------------------------------------------------------------------------------------------------------------------------------------------------------------------------------------------------------|------------------------------------------------------|-----------------------------------------------------------------------------------------------------------------------------------------------------------------------------------------------|-------------------------------------------------------------------------------------------------------------------------------------------------------------------------------------------------|

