|                                                                                                                                                                                                             | -Use of analgesics or anti-inflammatory drugs                                             |

Following the guidelines of the Federal Council of Dentistry for clinical care during the COVID-19 pandemic, the following protocol will be adopted: patients will be scheduled at staggered times to avoid crowding; 70% alcohol solution will be available in waiting areas for hand hygiene; face masks will be mandatory; the clinical environment will be disinfected between appointments from the least contaminated to the most contaminated areas (reflector handle, chair, stool, assistant cart surface, and dental unit, respectively); PVC barriers will be applied to contact surfaces (mechanical buttons, reflector handles, chair backrests and armrests, stool backrest, handpieces, three-way syringe body, and suction tips); all instruments will be disinfected with enzymatic detergent and sterilized.

Researchers will wear impermeable disposable gowns, disposable caps, protective goggles, surgical masks (for non-aerosol procedures), PPF or N95 masks (for aerosol-generating procedures), face shields, and gloves, all changed after each appointment. Regarding air-jet sensitivity testing in root exposures, relative isolation with cotton rolls will be used, and adjacent teeth will be covered with insulating tape (Isotape, TDV Dental, Pomerode, Santa Catarina, Brazil). The stimulus will consist of an air jet delivered by a three-way syringe positioned 1 cm from the cervical region for a maximum of 2 s. Immediately afterward, patients will indicate sensitivity level on the VAS, which consists of a 10 cm horizontal line where pain is scored from 0 to 10 points: 0 = no pain, 1–3 = mild pain, 4–6 = moderate pain, and 7–10 = severe pain. Patients will mark a vertical line across the horizontal scale to indicate DH intensity. The distance in mm from the zero endpoint will be measured with a millimeter ruler. Teeth with at least grade 3 sensitivity on the VAS will be included.

After selection, each patient will receive and sign an informed consent form (in duplicate), detailing study objectives and procedures.

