The CoVAS will then be used by applying a constant air-jet stimulus, 10 mm from the vestibular surface of the teeth, for 15 s. During this period, the patient will record discomfort intensity on a 0–100 scale using a manually controlled potentiometer. Sensitivity analyses (VAS and CoVAS) will be recorded at baseline. All participants will receive a soft-bristle toothbrush and a non-desensitizing toothpaste for use throughout the study.

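### Blinding stops at the volunteers, the VAS air jet is capped but not fixed in length, and the VAS mark is read by an unmasked person, so knowledge of allocation can reach the VAS by a route that is cheap to close

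*Protocol*

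**What the plan says.** Protocol section 3.1 limits masking in one sentence: "Only the volunteers will remain blinded to the allocation group (single-blind design". No masked or independent assessor is named elsewhere.

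Section 3.2 describes the two measurements.

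- **VAS.** The stimulus is an "air jet delivered by a three-way syringe positioned 1 cm from the cervical region for a maximum of 2 s". Then, "Immediately afterward, patients will indicate sensitivity level on the VAS", which is "a 10 cm horizontal line where pain is scored from 0 to 10 points". The reading is manual: "The distance in mm from the zero endpoint will be measured with a millimeter ruler". Neither the person delivering the jet nor the person reading the ruler is named.
- **CoVAS.** The stimulus is a "constant air-jet stimulus, 10 mm from the vestibular surface of the teeth, for 15 s", and the patient records discomfort with a hand-operated potentiometer.

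Section 3.5 repeats both scales at 7, 15 and 30 days and at 6 and 12 months. The sample size in section 3.2 rests on an "expected mean difference in cervical dentin hypersensitivity levels (measured by VAS) of 0.210 after six months", with no unit given. The schedule in section 4 places the analysis of data up to 30 days (Step C) in months 5 and 6, and the 6- and 12-month evaluations (Step D) in months 6 to 12.

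**The concern.** Blinding the patient protects the patient's own judgement. It does not protect the stimulus that the patient judges, or the handling of the mark afterwards. On the VAS, staff who may know the product deliver a jet with an upper time limit but no set or minimum length, and staff who may know the product convert the mark to a number. Allocation can enter on both sides of the patient's response.

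The first null hypothesis in section 2, no difference among protocols at each time point, is tested on these follow-up readings. A systematic difference between arms in how the stimulus is given or read does not average out with more teeth and cannot be removed after collection. Step C adds a route: nothing in the protocol keeps by-arm 30-day results from the people who will take the six-month readings, and six months is the time point used for the sample size.

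**Working it through.** **1. Where allocation knowledge can enter.**

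| Step | VAS | CoVAS |
|---|---|---|
| Length of jet | capped at 2 s, not fixed | constant, 15 s |
| Who gives the response | blinded patient | blinded patient |
| How it becomes a number | ruler, reader not masked | patient-operated potentiometer, 0–100 |
| Masked operator named | no | no |

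Open duration and manual reading therefore concern the VAS only. For CoVAS a residual risk remains, such as aim or cueing. Baseline readings precede randomization, since VAS is a stratification variable (section 3.3). The exposed readings are those at follow-up: up to 192 teeth × 5 visits = 960 VAS readings.

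**2. Size of the planned difference.** If 0.210 is in points on the 0–10 scale, it is 0.210 × 10 = 2.1 mm on the 10 cm line.

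**3. The protocol's own sample size.** Inputs from section 3.2: difference d = 0.210, α = 0.05, power 0.80, n = 48 per group. No SD is given, so 48 cannot be reproduced; only the SD that it implies can be found. For two means, two-sided, without dropout:

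SD = d × √(n/2) / (1.960 + 0.842) = 0.210 × 4.899 / 2.802 ≈ 0.367.

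If the stated 20% dropout was already included (38 to 39 evaluable teeth per group), the implied SD is about 0.33.

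**4. Effect of a systematic shift, for illustration.** Assume no true difference, 48 independent teeth per arm, a two-sided 5% comparison of two means, and a shift b between arms. SE = SD × √(2/48) = SD × 0.2041. The false-positive rate is P(Z > 1.96 − b/SE) + P(Z < −1.96 − b/SE).

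| SD (points) | SE | b = 0.21 | b = 0.10 |
|---|---|---|---|
| 2 (assumed) | 0.408 | 8.1% | 5.7% |
| 1 (assumed) | 0.204 | 17.7% | 7.8% |
| 0.367 (implied) | 0.075 | 80% | 27% |

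The 80% follows by construction: a bias equal to the planned difference is declared significant as often as a true effect of that size, which is the planned power. The shifts are assumptions, not estimates.

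**The case against.** Single-blinding is openly declared. It is neither an error nor a contradiction, and a patient-marked scale with a blinded patient is a real safeguard. That stands, and it makes this an improvement rather than a correction of a mistake.

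A reader might infer more than the protocol supports:

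- **That expectation moves the VAS by as much as 0.210.** The documents give no relation between jet time and score, no SD and no assessor-bias figure, so this cannot be derived.
- **That the examiner holds the syringe and may stop the jet at will.** The operator is not named, and a cap does not say who may stop or why. It is a reasonable inference, not stated text.
- **That CoVAS is exposed to the same degree.** Its jet is constant for 15 s and the patient records the response. VAS and CoVAS are also listed together as response variables, with neither named as primary.
- **That ruler reading alone could produce the planned difference.** Rounding to the nearest millimetre moves a reading by at most 0.5 mm, or 0.05 points, under a quarter of 0.210.

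Three further objections have force. All four arms are active, so between-arm bias needs different expectations of different products, and the direction is unknown. Section 3.6 plans tests of two proportions, so the rates above are not error rates of the stated analysis. And at an SD of 2 a true 0.210 effect would itself be detected only about 8% of the time, so that row also reflects how little such a sample can show.

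None of this supplies a masked reader or a fixed jet length. The 15 s CoVAS jet shows that the protocol can fix a duration where it chooses to.

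**Conclusion.** The point holds as an avoidable weakness in how the VAS is obtained. The protocol restricts masking to the volunteers, leaves the VAS jet length open below 2 s, and names no masked reader; CoVAS is less exposed. The size and direction of any bias are unknown. What can be said is that a trial planned around 0.210 leaves little room for measurement bias if that figure is in VAS points: a shift of that size would give about 8%, 18% or 80% false positives at SDs of 2, 1 or 0.37. These rates assume a comparison of means, independent teeth and 48 per arm. The SDs of 2 and 1 are assumptions; 0.37 is implied by the protocol's inputs with a two-sided test and no dropout. The change is worth making because it is cheap and the bias cannot be repaired afterwards.

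**What to change.** Replace the sentence "Only the volunteers will remain blinded to the allocation group (single-blind design" and state that:

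1. the VAS jet is delivered for one uniform, timed duration at every tooth and visit, and any early stop is recorded;
2. VAS sheets carry a tooth code only and are measured without access to the allocation list;
3. the analysis, including the 30-day analysis, is run with coded arms, and by-arm results are withheld from those who make later assessments;
4. where the existing team allows, the person who applied the product does not deliver the follow-up stimulus to that tooth and does not see its allocation or earlier scores.

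When the stimulus is standardized, the jet distance must also be reconciled: Table 2 gives 10 cm and the text of section 3.2 gives 1 cm.

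Items 1 to 3 need protocol wording and some coding work, but no extra staff or procedures. Item 4 is conditional because the protocol does not state the team size, and it leaves less freedom in scheduling. Masking of the operator may be imperfect if a coating is visible; items 1 to 3 help regardless.

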### 3.2 Sample Size Calculation and Patient Selection

Sample size was calculated based on a published study using Sigma Plot 12.0 software, with an expected mean difference in cervical dentin hypersensitivity levels (measured by VAS) of 0.210 after six months. Test details: significance level ( $\alpha$ ) = 0.05; test power ( $1-\beta$ ) = 0.80; dropout ( $\beta$ ) = 0.2. The final sample size was determined as 48 teeth per group.

Patients will be recruited from the undergraduate clinic of FOA-UNESP, aged between 20 and 70 years, with at least one root exposure, totaling 192 teeth with DH in non-cavitated root exposures (not requiring restoration), regardless of location in the dental arch. Teeth will be divided into three groups ( $n = 48$  teeth each) with a 5% significance level. Eligibility criteria are described in Table 2.

**Table 1.** Products to be used in the study and their composition according to the manufacturers

| Material                                                                                                                                                                                                                                                                          | Manufacturer                                  | Composition*                                                                                                                                                                           | Application*                                                                                                                                                                             |
|------------------------------------------------------------------------------------------------------------------------------------------------------------------------------------------------------------------------------------------------------------------------------------------|------------------------------------------------------|-----------------------------------------------------------------------------------------------------------------------------------------------------------------------------------------------|-------------------------------------------------------------------------------------------------------------------------------------------------------------------------------------------------|
| Duraphat (VF)                                                                                                                                                                                                                                                                     | Colgate-Palmolive Company®                           | NaF 5% (22,600 ppm); colophony; ethanol; shellac; mastic; saccharin; flavoring; white wax; beeswax                                                                                            | A thin layer will be applied with a microbrush on the clean and dry surface; stable for 10 minutes.                                                                                             |
| Biosilicate® (SS)                                                                                                                                                                                                                                                                 | Vitrovita, Institute of Innovation in Vitroceramics® | Solution 1:10 of P (1–10 µm) and distilled water. Elements: P 2 O 5 ; Na 2 O; CaO; SiO 2                                                          | A thin layer will be applied with a microbrush on the clean and dry surface. The solvent will be evaporated for 5 s and then rubbed for 20 s. Finally, light curing will be performed for 10 s. |
| Single Bond Universal (SB)                                                                                                                                                                                                                                                        | 3M ESPE, Dental Products®                            | Ethanol; BISGMA; Silane treated with methacrylate; HEMA; Copolymer of acrylic and itaconic acid; UDMA; Water; Dipentaerythritol pentaacrylate phosphate; Initiator                            | A thin layer will be applied with a microbrush on the clean and dry surface. The solvent will be evaporated for 5 s and then rubbed for 20 s. Finally, light curing will be performed for 10 s. |
| PRG Barrier Coat (VB)                                                                                                                                                                                                                                                             | Shofu INC.®                                          | S-PRG (3.0 µm) based on distilled water; fluoroboroaluminosilicate glass; methacrylic acid monomer; phosphonic acid monomer; Bis-MPEPP; carboxylic acid monomer; TEGDMA; initiator and others | A drop of activator will be mixed in the capsule. The mixture will be applied with a disposable brush in a thin layer on the surface, dried for 3 s, and then light cured.                      |
| Abbreviations: TMP (sodium trimetaphosphate nanoparticle); TEGDMA (triethylene glycol dimethacrylate); BISGMA (bisphenol A diglycidyl ether dimethacrylate); HEMA (2-hydroxyethyl methacrylate); UDMA (urethane dimethacrylate); Bis-MPEPP (bisphenol A polyethoxy methacrylate). |                                                      |                                                                                                                                                                                               |                                                                                                                                                                                                 |
| *According to manufacturers: de Melo Alencar et al. (2019)  ; Fujimoto et al. (2010)  .                                                                                                                                                                         |                                                      |                                                                                                                                                                                               |                                                                                                                                                                                                 |

**Table 2.** Inclusion and exclusion criteria for patients

| Inclusion Criteria                                                                                                                                                                                   | Exclusion Criteria                                                                 |
|-------------------------------------------------------------------------------------------------------------------------------------------------------------------------------------------------------------|-------------------------------------------------------------------------------------------|
| -Age between 20–70 years, regardless of sex                                                                                                                                                                 | -Pregnant, lactating, or smoking patients                                                 |
| -Good general health; no history of allergies to dental products                                                                                                                                            | -Presence of active caries lesions                                                        |
| -Presence of at least one non-cavitated root exposure ( $\geq 1$ mm depth, not requiring restoration) presenting dentin hypersensitivity of at least grade 3 (VAS) to air-jet stimulation at 10 cm distance | -Use of desensitizing agents in the last 6 months                                         |
| -Absence of active periodontal disease                                                                                                                                                                      | -Active periodontal disease without treatment                                             |
|                                                                                                                                                                                                             | -Use of orthodontic appliances or removable prostheses with clasps on the evaluated tooth |
|                                                                                                                                                                                                             | -Parafunctional habits and occlusal trauma                                                |
|                                                                                                                                                                                                             | -Use of analgesics or anti-inflammatory drugs                                             |

Following the guidelines of the Federal Council of Dentistry for clinical care during the COVID-19 pandemic, the following protocol will be adopted: patients will be scheduled at staggered times to avoid crowding; 70% alcohol solution will be available in waiting areas for hand hygiene; face masks will be mandatory; the clinical environment will be disinfected between appointments from the least contaminated to the most contaminated areas (reflector handle, chair, stool, assistant cart surface, and dental unit, respectively); PVC barriers will be applied to contact surfaces (mechanical buttons, reflector handles, chair backrests and armrests, stool backrest, handpieces, three-way syringe body, and suction tips); all instruments will be disinfected with enzymatic detergent and sterilized.

Researchers will wear impermeable disposable gowns, disposable caps, protective goggles, surgical masks (for non-aerosol procedures), PPF or N95 masks (for aerosol-generating procedures), face shields, and gloves, all changed after each appointment. Regarding air-jet sensitivity testing in root exposures, relative isolation with cotton rolls will be used, and adjacent teeth will be covered with insulating tape (Isotape, TDV Dental, Pomerode, Santa Catarina, Brazil). The stimulus will consist of an air jet delivered by a three-way syringe positioned 1 cm from the cervical region for a maximum of 2 s. Immediately afterward, patients will indicate sensitivity level on the VAS, which consists of a 10 cm horizontal line where pain is scored from 0 to 10 points: 0 = no pain, 1–3 = mild pain, 4–6 = moderate pain, and 7–10 = severe pain. Patients will mark a vertical line across the horizontal scale to indicate DH intensity. The distance in mm from the zero endpoint will be measured with a millimeter ruler. Teeth with at least grade 3 sensitivity on the VAS will be included.

After selection, each patient will receive and sign an informed consent form (in duplicate), detailing study objectives and procedures.

The CoVAS will then be used by applying a constant air-jet stimulus, 10 mm from the vestibular surface of the teeth, for 15 s. During this period, the patient will record discomfort intensity on a 0–100 scale using a manually controlled potentiometer. Sensitivity analyses (VAS and CoVAS) will be recorded at baseline. All participants will receive a soft-bristle toothbrush and a non-desensitizing toothpaste for use throughout the study.

